**Methods:**

EANITIATE is a Danish, open, prospective, multicenter, randomized (1:1), parallel group study in patients with new-onset diabetes following treatment with glucocorticoids (> 20 mg equivalent prednisolone dose/day) with blinded endpoint evaluation (PROBE design). Included patients are randomized to either a Sodium-Glucose-Cotransporter 2 (SGLT2) inhibitor or neutral protamin Hagedorn (NPH) insulin and followed for 30 days. Blinded continuous glucose monitoring (CGM) will provide data for the primary endpoint (mean daily blood glucose) and on glucose fluctuations in the two treatment arms. Secondary endpoints are patient related outcomes, hypoglycaemia, means and measures of variation for all values and for time specific glucose values. This is a non-inferiority study with the intent to demonstrate that treatment with empagliflozin is not inferior to treatment with NPH insulin when it comes to glycemic control and side effects.

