## Methods/design

### Aims

Our study is designed to test the safety and efficacy of empagliflozin for the treatment of GIDM compared to neutral protamine Hagedorn (NPH) insulin. The hypothesis is that empagliflozin can be used as a safe alternative to NPH insulin in patients with GIDM. The primary aim is to compare mean glucose level (primary endpoint, measured by continuous glucose monitoring (CGM)) between empagliflozin and NPH insulin treatment groups, with a tolerated significant difference in mean daily glucose of up to 2 mmol/L to the higher side.

Secondary endpoints are 9 other CGM metrics, based on recommendations endorsed internationally (American Diabetes Association, American Association of Clinical Endocrinologists, American Association of Diabetes Educators, European Association for the Study of Diabetes, Foundation of European Nurses in Diabetes, International Society for Pediatric and Adolescent Diabetes, JDRF, and Pediatric Endocrine Society) [11], Self-Monitoring of Blood Glucose (SMBG) -related outcomes, and patient-related outcomes.

Tertiary outcome is cost-effectiveness of empagliflozin compared to NPH-insulin in treating GIDM.

Further predefined study aims are exploratory and include differences between treatment groups in relation to HbA_1c_, fructosamine, performance status [12].

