### Definition of endpoints

#### Primary objective

To determine if empagliflozin can be used as a safe alternative to NPH insulin in patients with GIDM, with a tolerated significant difference in mean daily glucose (mean of CGM measurements) of up to 2 mmol/L to the higher side. Outcome measure: Mean glucose difference between the empagliflozin and NPH insulin group (calculated mean of CGM glucose profiles over the 2 first weeks of treatment). Calibration capillary glucoses values will be recorded. 70% of possible data (10 out of 14 days or 2822 out of 4032 possible tests) should be available for the patient to be included in the statistical analysis [11].

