### Statistics

#### Power

A total of 74 patients should be included to allow randomization of approximately 37 patients in each arm, and for at least 29 patients to complete 30 days of treatment per arm, with alpha set to 0.05 and beta 0.90. It is estimated that a total of 58 completing patients can provide 90% power to detect a significant difference (two-tailed p-value ≤0.05) between the two treatments in reduction of plasma glucose, if there is a true difference of 2 mmol/L (non-inferiority limit) with a standard deviation (SD) for plasma glucose of 2.6 mmol/L. In our own recent study, which included 1131 blood glucose measurements in patients with newly diagnosed GIDM, we found an SD of 4.2 mmol/L [13]. In another study with 21 patients that developed GIDM after prednisolone, an SD of 1 mmol/L was calculated [28]. Thus, because the true SD for glucose for GIDM is not known, the SD used for the power calculation was pragmatically calculated as a mean from the 2 studies.

It is expected that up to 16 patients (25%) may leave the study prematurely, thus a total minimum of 74 patients will be included and at least 58 complete the study.

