#### Primary analysis

A comparison between groups of differences in mean daily plasma glucose from 14-day CGM using a T-test with a 95% confidence interval. If we, based on the primary analysis, can be 95% sure that the biggest difference in glucose is not more than 2 mmol/L then non-inferiority for the experimental arm (empagliflozin) is concluded.

Subgroup analysis will be done with ANOVA, which will include stratification on dose of glucocorticoids and more.

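### The non-inferiority rule names neither direction nor confidence limit, and the stated 90% power with 58 completers holds only at one-sided 0.05, not under the plan's two-sided 95% interval (about 82%)

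*Protocol article*

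**What the plan says.** The Methods part of the abstract sets the frame: "This is a non-inferiority study with the intent to demonstrate that treatment with empagliflozin is not inferior to treatment with NPH insulin". The Aims fix a margin and a direction, "with a tolerated significant difference in mean daily glucose of up to 2 mmol/L to the higher side", and the Primary objective repeats both for the mean of the CGM readings over the first two weeks.

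The decision rule is in the Primary analysis section. The groups are compared by a t-test with a 95% confidence interval, and if the investigators "can be 95% sure that the biggest difference in glucose is not more than 2 mmol/L then non-inferiority" of the empagliflozin arm is concluded. That sentence gives no order of subtraction and names no confidence limit. The Data presentation section makes every test two-tailed at 0.05.

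The Power section says that 58 completing patients, 29 per arm, give "90% power to detect a significant difference (two-tailed p-value ≤0.05) between the two treatments in reduction of plasma glucose". The condition is a true difference of 2 mmol/L, which the section labels as the non-inferiority limit, with an SD of 2.6 mmol/L.

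**The concern.** Two things in these sections do not fit together.

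The first is the decision sentence. The margin has a direction in the Aims and Primary objective, but the sentence that will be applied to the data does not repeat it. Nor does it say whether 95% confidence belongs to a two-sided interval (2.5% error on the side that matters) or to a one-sided bound (5% error on that side).

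The second is the power statement. It describes detecting a difference, with the true difference set equal to the margin. In a non-inferiority trial, a true difference at the margin on the harmful side is the null hypothesis. The quantity needed is the chance of showing non-inferiority at an assumed true difference, usually 0, and the section never states that assumption. It also speaks of a reduction in plasma glucose, whereas the primary endpoint is the on-treatment 14-day CGM mean. The sensor is attached at visit 1, the randomisation visit, so there is no earlier CGM period from which to measure a reduction.

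At stake are the trial's main conclusion in a borderline case and the power figure on which recruitment rests.

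**Working it through.** **Inputs.** Margin 2 mmol/L (Aims, Primary objective, Power); SD 2.6 mmol/L and 29 completers per arm (Power); two-tailed 0.05 (Power, Data presentation); t-test with 95% interval (Primary analysis). The Power section's beta of 0.90 is read as 90% power. The true difference under which non-inferiority is to be shown is not given; 0 is assumed, with +0.5 mmol/L as a second case.

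**Step 1: reproduce the plan's 29 per arm.** Normal formula: n per arm = 2 × (z_alpha + z_power)² × SD² / 2², where SD²/2² = 6.76/4 = 1.69.

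- Two-sided 0.05 as stated: 2 × (1.960 + 1.282)² × 1.69 = 35.5, so 36 per arm (72 in total).
- Non-inferiority at one-sided 0.025, true difference 0: the same formula, so again 36 per arm.
- One-sided 0.05: 2 × (1.645 + 1.282)² × 1.69 = 28.95, so 29 per arm.

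Only one-sided 0.05 returns the plan's figure. With the t distribution the numbers are 37 per arm (two-sided 0.05) and 30 per arm (one-sided 0.05).

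**Step 2: power of 29 per arm.** Standard error = 2.6 × √(2/29) = 0.683 mmol/L.

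| True difference (empagliflozin minus NPH) | Rule | Normal approximation | t-based |
|---|---|---|---|
| 0 | upper limit of two-sided 95% CI below +2 | Φ(2/0.683 − 1.960) = Φ(0.97) = 83% | 82% |
| 0 | one-sided 95% bound below +2 | Φ(2/0.683 − 1.645) = Φ(1.28) = 90% | 89% |
| +0.5 | upper limit of two-sided 95% CI below +2 | Φ(1.5/0.683 − 1.960) = Φ(0.24) = 59% | 58% |

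**Step 3: where the reading of the rule changes the verdict.** With 56 degrees of freedom and an observed SD of 2.6:

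- Two-sided 95% interval: half-width 2.003 × 0.683 = 1.37, so the largest observed difference that passes is 2 − 1.37 = 0.63 mmol/L.
- One-sided 95% bound: distance 1.673 × 0.683 = 1.14, so the largest that passes is 2 − 1.14 = 0.86 mmol/L.

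An observed difference of +0.75 has an upper limit of 2.12 under the first reading (fails) and 1.89 under the second (passes). The affected zone, about 0.63 to 0.86 mmol/L, lies where empagliflozin looks worse than NPH insulin, so the looser reading favours the experimental arm.

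**The case against.** The strongest reply is that the rule is clear in context. The trial is called a non-inferiority study, the margin is on the higher side, and the decision sentence itself concludes non-inferiority for empagliflozin. The largest difference one can be 95% sure of is then a lay description of the upper limit of the interval named in the sentence before it. Most of this stands: the upper limit of the two-sided 95% interval is the natural reading.

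A reader might infer that the article holds three rival decision rules, one of them an equivalence rule with both limits inside ±2 mmol/L. An observed difference of −1.0 (95% interval −2.37 to +0.37) would then fail even though it favours empagliflozin. The document does not support this. Equivalence is nowhere its aim, and the Power section decides nothing about the result.

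A reader might also infer that the power is really 2.5%, because that is how often a non-inferiority test succeeds when the true difference equals the margin. This takes the loose wording too literally. The Power section labels the 2 mmol/L as the non-inferiority limit, and Step 1 shows that a two-sided 0.05 calculation at that distance gives the same size as non-inferiority at one-sided 0.025 with true difference 0. The wording alone does not spoil the sample size.

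Finally, a detailed analysis plan is promised before the randomisation code is added, and it could name the limit and direction. It cannot remove the conflict between a 90% claim that needs one-sided 0.05 and the two-tailed tests and 95% interval printed in the same article.

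**Conclusion.** The point holds in a limited form. The decision sentence should name the direction and the limit. The sections quoted favour one reading, but the sample size matches the other error level, so the choice is not wholly academic: it decides the verdict for observed differences of about 0.63 to 0.86 mmol/L.

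The stated power is wrong for the stated test. Under a two-sided 95% interval, 58 completers give about 82% at a true difference of 0, not 90%. The 90% figure requires one-sided 0.05, which contradicts the Power, Data presentation and Primary analysis sections.

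These figures take the plan's SD of 2.6 mmol/L and 29 evaluable patients per arm as given. The zone of changed verdicts also assumes that the observed SD equals 2.6.

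**What to change.** In Primary analysis, replace the decision sentence with: Non-inferiority is concluded if the upper limit of the two-sided 95% CI for empagliflozin minus NPH in 14-day CGM mean glucose is below +2 mmol/L.

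In Power, replace the language of detecting a difference, and the reference to a reduction in plasma glucose, with the power to show non-inferiority on the 14-day CGM mean at a true difference of 0. State it as about 82% for 58 completers, with 58% at +0.5 mmol/L as a sensitivity case.

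This needs no new data. Its cost is that the stated power becomes less favourable. If the sponsor wants to keep 90%, about 72 (normal) to 74 (t-based) completers are needed instead of 58, which means more patients. At the plan's own loss of 16 in 74, 72 completers would need 72 / (1 − 16/74), or about 92 randomised. The rule should be fixed before the randomisation code is added to the dataset, as the Statistical analysis plan section already foresees for the full plan.

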#### Secondary analysis

Continuous variables analysis will be done using a T-test. For categorical outcomes a Chi-square test will be used.

#### Tertiary analysis

Incremental cost–effectiveness ratio (ICER) analysis will be conducted. The incremental costs associated with empagliflozin and NPH insulin will be compared with the incremental outcomes. Intention to treat (ITT) and per protocol (PP) analysis will both be analysed.

## Discussion

EANITIATE is the first combined in-hospital and outpatient study to compare an SGLT2 inhibitor with NPH insulin to treat GIDM. This novel approach to management of glucocorticoid-induced hyperglycemia has not been tested before and if SGLT2 inhibition with empagliflozin compared to NPH insulin is a safe, effective and resource sparing treatment for GIDM, it has the potential to improve the situation for affected patients. Furthermore, it could have health economic benefits.

## Data Availability

The datasets used and/or analysed during the current study are available from the corresponding author on reasonable request.

## Abbreviations

AE: Adverse events
ALAT: Alanine aminotransaminase
ASAT: Aspartate aminotransferase
AUC: Area under the curve
BP: Blood pressure
CGM: Continuous glucose monitoring
CRF: Case report form
CRP: C-reactive protein
CV: Coefficient of variation
DKA: Diabetic ketoacidosis
EU: European union
GCP: Good clinical practice
GIDM: Glucocorticoid-induced diabetes mellitus
GC: Glucocorticoid
HHS: Hyperosmolar hyperglycaemic state
HRQL: Health-related quality of life
ICF: Informed consent form
ICH-GCP: International conference on harmonisation-good clinical practice
IP: Investigational product
LDH: Lactate dehydrogenase
MAGE: Mean amplitude of glycemic excursions
MCV: Middle cell volume
MCS: Mental component summary
MD: Medical doctor
NPH: Neutral protamine hagedorn
P: Pulse
PCS: Physical component summary
PRO: Patient-related-outcome
PROBE: Prospective randomized open blinded end-point
SAE: Serious adverse events
SD: Standard deviation
SF-36: Short form 36
SP: Sundhedsplatformen (Electronic patient records)
TAR: Time above range
TBR: Time below range
TIR: Time in range
VAS: Visual analogue scale
VEK: The regional committee on biomedical research ethics
